#### 2.3.1 Online survey of sex workers

There is no existing, robust international survey instrument concerning sex workers, sexual violence and legal consciousness.

Experiences of sexual violence in sex work are under-researched and differ from standard data measuring sexual violence (for example, many sexual violence statistics are gathered using women only, and most sexual violence data are gathered about violence by intimate partners, rather than strangers or acquaintances, and do not contain information about transactional sex or sex in a workplace). Unfortunately, standard sexual violence surveys do not include samples from New Zealand. Therefore, a new pilot survey instrument is required for this project.

#### 2.3.2 Survey design

The online survey for this study has been iteratively through 11 drafts, developed from existing instruments, adapted for relevance to sex working populations in the study sites, with pilot elements added.

The initial draft consulted existing surveys from Survivors UK, West Cork Health Authority, The NI Department of Justice, Criminalisation of Paying for Sex Survey [25], Beyond the Gaze Online Sex Work Survey [26] and the Evaluation of Protection From Abuse (Sc) Act 2001 survey [27]. Each draft was reviewed by the research team, with three drafts written in consultation with Expert Advisory Boards in each site and an Academic Advisory Group. The consulting statistician reviewed two drafts.

The final survey utilises adapted existing victimisation survey items from the Crime Survey of England & Wales Self Completion Module: Domestic Abuse, Sexual Victimisation and

Stalking Module [28], with methodological adaptations from Walby & Towers [29] and the National Intimate Partner and Sexual Violence Survey [30]. In addition, questions for sex workers were adapted from the context of sex workers’ condom use study [31], to begin to elucidate consciousness of sexual consent.

Novel and exploratory questionnaire items were added to be relevant to sex-working populations in the study sites and to reflect the particularity of the legal context in each area. Some questions from the Beyond the Gaze [32,33] project and in Northern Ireland [34] were added. Site specific scales for different jurisdictions (comprising no more than 20% difference between surveys) were added, for example to align ethnicity and income categories with national data in the sites. Income demographics were harmonised across the sites using OECD methodology [35], and all categories were taken from 2019 existing instruments, to assist comparability across the sites.

The survey was piloted with members of Advisory Boards, sex workers and other NGOs, using test-retest methodology [36]. This was conducted to check that the questions–and their translations–accurately collect the data required, to improve the reliability of the survey instrument and minimise measurement error.

The survey will be launched in September 2022, with data gathered simultaneously in all sites. The survey will remain open until February 2023 (or until a sufficient sample size has been reached for statistical significance, within the time constraints of the study). The survey will be translated into Portuguese, South American (Brazilian) Spanish, Romanian, Filipino, Thai and Mandarin; these languages have been identified as the most crucial to reach migrant sex workers in the research sites.

Respondents will be recruited through the project Advisory Boards in each research site, adult sex work platforms and NGOs delivering outreach with sex workers, as well as via the broader project teams’ connections with sex work communities. Given the hard-to-reach nature of sex working populations and the sensitivity of sexual violence, random sampling methods are not appropriate for this study. Therefore, non-random strata sampling by sector and demographic group will be employed.

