#### 2.2.3 Study period

The study began in July 2021 and data collection is taking place across an estimated 11-month period from March 2022 to February 2023. The end date of survey data collection will depend on the point at which a sufficient sample is achieved for the survey in each jurisdiction.

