#### 2.3.5. Survey sample size

Despite the frequent experiences of violence in some forms of sex work, accessing workers with violent experiences among the entire population of sex workers can be challenging. This population is often under-represented in standard sexual violence surveys, which prevents weighting methodology being employed in this study–this is because there are not sufficient existing independent data with which to compare populations. In other sex work contexts, too many invitations to participate in studies targeted at a few individuals, stigma, and working without legal protection can mean some sex workers are reluctant to engage with research [37].

Unfortunately, the sample for this survey cannot be randomised, as too few responses would be received and there are no intervention arms in this study or reliable population estimates in the sites [38]. However, stratified sample groups for distribution by sector and site have been designed for the recruitment, to attempt to ensure as far as possible that no under- or over-representation of one particular sector of sex work in each research site.

To ensure that we achieve an adequate sample size, calculations were made to test our null hypothesis, namely that there is no difference in the experience of sexual violence by jurisdiction. We used the chi-squared test to test for independence of outcome (binary Yes, No) and jurisdiction (4 levels) with 3 degrees of freedom. Since a significance level of 5% is desired, the chi-squared statistic would need to exceed 7.81. To test the null hypothesis, a minimum sample size of 1760 respondents for the survey would be required, with a minimum of 440 respondents in each jurisdiction.

We derived an alternative hypothesis from a low conservative estimate from Deering et al [39], that circa 15% of sex workers experience violence. We anticipated the overall probability of sexual violence at 15% across all 4 jurisdictions, with 2 jurisdictions differing by 10 points (ie. one records 10% and the other 20%) to be detectable at least 80% of the time. We calculated that we would need a maximum sample size of 3200, where p = 55%. Fifty-five per cent was our upper estimate of sexual violence in sex work [40]. The chi-squared statistic was 7.84 from this calculation.

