#### 2.3.6. Survey data analysis

Survey data analysis will be conducted at mid- and endpoints of the data gathering phase. The mid-point analysis will enable further recruitment where a sample is insufficient and to produce indicative results to inform analysis.

Logistic regression will be used to test the study’s null hypothesis, that there is no significant difference in victimisation by the jurisdiction. In addition, we will assess whether action and harm are mediated by socio-demographic category (gender, ethnicity, age, sexual orientation, citizenship status, income/financial autonomy). Other variables included in the survey are: attitudes to policing, criminal justice response and access to support. Information on conditional consent specific to sex work will also be analysed–for example, under-payment/non-payment, condom removal (‘stealthing’)–as will situations in which consent could not be given; because of intoxication, for example.

Multivariate analysis will be used to identify clusters of respondents by experience of victimisation, jurisdiction and sex work sector with the aim of producing the first statistical international typology of respondent experiences of sexual violence (and justice/support after it) in sex work. Whilst our preference is to use either AHC (Agglomerative Hierarchal Clustering) or PCA (Principal Components Analysis) to generate the clusters, it is unlikely that all variables can be converted into numerical form. Should this not be possible, then our intention is to use Multiple Correspondence Analysis (MCA), which is capable of handling categorical variables. Once our clusters have been generated, we will then explore how they differ in terms of socio-demographic category (gender, ethnicity, age, sexual orientation, citizenship status and income) in different jurisdictions and sex work sectors.

Statistical analysis, reports and publications will be, wherever possible, in line with the SAMPL guidelines [41].

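### The survey's closing rule is worded around statistical significance and sits beside a mid-point look at results, so the protocol permits optional stopping

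*Protocol article*

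**What the plan says.** Three sections of the protocol article govern when the survey ends.

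- **Section 2.3.2 (Survey design)** gives a date, February 2023, and an alternative: "until a sufficient sample size has been reached for statistical significance". The alternative is limited by the study's time constraints.
- **Section 2.2.3 (Study period)** words the rule without significance: "The end date of survey data collection will depend on the point at which a sufficient sample is achieved", judged separately for each jurisdiction.
- **Section 2.3.6 (Survey data analysis)** plans two analyses, at the middle and the end of data gathering. Of the first it says: "The mid-point analysis will enable further recruitment where a sample is insufficient and to produce indicative results to inform analysis".

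The test at stake is the study's null hypothesis of no difference in victimisation by jurisdiction. Section 2.3.5 plans it as a chi-squared test of "independence of outcome (binary Yes, No) and jurisdiction (4 levels) with 3 degrees of freedom" and fixes the level: "Since a significance level of 5% is desired, the chi-squared statistic would need to exceed 7.81". Section 2.3.6 then says: "Logistic regression will be used to test the study’s null hypothesis".

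The survey size appears as 1,000 (Abstract and section 2.3, Work Package 1), as a minimum of 1,760 with 440 per jurisdiction, and as a maximum of 3,200 at a prevalence of 55% (both section 2.3.5). Section 2.3.5 closes by allowing that subgroup comparisons may need more respondents, or fewer if a suitable scale is found.

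**The concern.** A sample size can be planned to give a stated power, but it cannot be known to give significance until the test is run. Taken at its word, the section 2.3.2 rule therefore has someone test, look, and decide whether to keep recruiting. The mid-point analysis supplies an occasion for this: results are produced, and the same exercise decides whether recruitment continues.

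If that decision responds to the jurisdiction comparison, and each look is judged against 7.81, the chance of declaring a difference when none exists exceeds 5%. The hypothesis concerned is the one the study was set up to test, on a contested policy question. If readers cannot exclude result-driven closure from the protocol, later reassurance will carry little weight.

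**Working it through.** **1. The plan's own threshold.** The 95th percentile of chi-squared on 3 degrees of freedom is 7.815, so the stated 7.81 reproduces. It is the threshold for a single look.

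**2. Inputs.** Level 5%, 3 degrees of freedom and four jurisdictions (section 2.3.5); two analyses, middle and end (section 2.3.6); 15% prevalence everywhere under the null, which is the plan's overall rate. Assumed, because the article does not say: equal numbers per jurisdiction, mid-point at half the final sample, and a result beyond 7.81 at either look counting as rejection.

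**3. Statistic.** With n respondents per jurisdiction, observed proportions p_i and their mean p:

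T = n × Σ(p_i − p)² / [p(1 − p)]

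Under the null, T is approximately the squared length of a vector of three independent standard normals. Let Z be that vector at mid-point and Z′ an independent one for the second half of the data. Then T₁ = |Z|² and T₂ = |(Z + Z′)/√2|². The error sought is P(T₁ > 7.815 or T₂ > 7.815). A logistic regression with jurisdiction as the only factor gives a 3-degree-of-freedom test that is equivalent in large samples, so the result carries over.

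**4. Results by simulation under the null.**

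| Closing behaviour | Type I error |
|---|---|
| One look | 5.0% |
| Closure by count only (250 to 440 per site, independent of outcome) | 4.99% |
| Two equal looks, 7.81 at each (normal approximation, 1,000,000 runs) | 8.5% |
| Same, binomial data at 15%, final N = 1,000 | 8.4% |
| Same, binomial data at 15%, final N = 1,760 | 8.3% |
| Looks at 1,000 and 1,760 (first at 1,000/1,760 = 57% of the data) | 8.2% |

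As a sanity check, two independent tests would give 1 − 0.95² = 9.75%. The looks share data, so the answer must lie between 5% and 9.75%.

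**5. Threshold that would hold 5%.** The 95th percentile of max(T₁, T₂) is 9.03, which corresponds to a nominal p of 0.029 at each of two equal looks.

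**6. Is there one count that defines sufficient?** No. The article states 1,000, 1,760 and 3,200. Nor does the calculation single out 1,760. With jurisdictions at 10%, 15%, 15% and 20% (the two unnamed sites taken as 15%), the 3-degree-of-freedom test needs about 1,113 in total for 80% power, and 1,760 gives 95.1%. That mismatch is a separate matter and the conclusion here does not depend on it.

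**The case against.** The strongest reply is that the section 2.3.2 phrase is loose wording for an adequately powered sample. What has to be sufficient there is a sample size, not a p-value. The same sentence gives a calendar date and a time cap. Section 2.2.3 restates the rule with no mention of significance, section 2.3.5 derives counts from level, power and effect, and section 2.3.6 ties extra recruitment to an insufficient sample, not to a disappointing result. No section says that the jurisdiction test is run at mid-point, or that a significant result closes the survey. Much of this stands, and it is why the inflation is conditional.

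It does not remove the problem. The benign reading needs one count fixed in advance, and the article offers three. Nothing bars the person who judges sufficiency from using the indicative results.

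A reader might infer more than the documents support:

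- **That the 5% level is certainly inflated.** Closure by count leaves it at 5%, and the text is compatible with that.
- **That the error reaches 11%, 16% or 28%.** Those figures need looks at 1,000, 1,760 and 3,200, or six looks, or twenty-four. Only two analyses are planned, and 3,200 belongs to a different prevalence assumption; it is not an extension step.
- **That outcomes will decide which site keeps recruiting.** Section 2.2.3 speaks of sample achieved per jurisdiction, and topping up thin sites fits the stratified recruitment.
- **That analyses will be chosen after seeing results.** Section 2.3.6 names them in advance, and its one contingency turns on variable type.

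It is also fair to say that in a non-random, self-selected sample this is not the largest threat to inference.

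**Conclusion.** The point holds as a defect of wording that permits optional stopping; it is not proof that optional stopping is planned. If the survey could close, or the null be rejected, on an unadjusted 5% test at either planned analysis, type I error would be about 8.5% (8.2% to 8.5% across the variants checked). If closure rests on counts and date alone, it is 5%. The higher figure assumes equal allocation, a mid-point at about half the data, and rejection allowed at either look. The article neither states nor excludes that last condition.

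**What to change.** - In section 2.3.2, replace the reference to statistical significance with one named target count per jurisdiction. Bring sections 2.2.3 and 2.3.5, Work Package 1 and the Abstract into line with it.
- State that the survey closes at that count or in February 2023, regardless of results.
- In section 2.3.6, base mid-point recruitment decisions only on response counts by site, sector and demographic group.
- Run the jurisdiction test once, at the end. If victimisation by jurisdiction is to be tested at mid-point, adjust the threshold: about p = 0.029 at each of two equal looks (critical value about 9.03 in place of 7.81).

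The cost is a change of wording, plus either no mid-point result on the main hypothesis or a stricter threshold for it. Descriptive indicative results may stay, provided they do not affect closure. The change should be in place before anyone sees mid-point results.

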#### 2.3.3 Survey platform

Microsoft Office Forms was chosen as the platform for the survey, as it meets GDPR data protection requirements and has secure storage to meet regulations in all the research sites. It has accessible audio plugins to read questions and a design that enabled the use of translations into different languages required in the research sites.

#### 2.3.4 Survey eligibility criteria

Survey respondents are sex workers or people who have exchanged sex for something of value (e. g. accommodation, substances, gifts) and who;

Are over 18 years old;Have sold or exchanged sex in one of the study regions (New Zealand, Nevada, USA, ESW and/or Northern Ireland).

#### 2.3.5. Survey sample size

Despite the frequent experiences of violence in some forms of sex work, accessing workers with violent experiences among the entire population of sex workers can be challenging. This population is often under-represented in standard sexual violence surveys, which prevents weighting methodology being employed in this study–this is because there are not sufficient existing independent data with which to compare populations. In other sex work contexts, too many invitations to participate in studies targeted at a few individuals, stigma, and working without legal protection can mean some sex workers are reluctant to engage with research [37].

Unfortunately, the sample for this survey cannot be randomised, as too few responses would be received and there are no intervention arms in this study or reliable population estimates in the sites [38]. However, stratified sample groups for distribution by sector and site have been designed for the recruitment, to attempt to ensure as far as possible that no under- or over-representation of one particular sector of sex work in each research site.

To ensure that we achieve an adequate sample size, calculations were made to test our null hypothesis, namely that there is no difference in the experience of sexual violence by jurisdiction. We used the chi-squared test to test for independence of outcome (binary Yes, No) and jurisdiction (4 levels) with 3 degrees of freedom. Since a significance level of 5% is desired, the chi-squared statistic would need to exceed 7.81. To test the null hypothesis, a minimum sample size of 1760 respondents for the survey would be required, with a minimum of 440 respondents in each jurisdiction.

We derived an alternative hypothesis from a low conservative estimate from Deering et al [39], that circa 15% of sex workers experience violence. We anticipated the overall probability of sexual violence at 15% across all 4 jurisdictions, with 2 jurisdictions differing by 10 points (ie. one records 10% and the other 20%) to be detectable at least 80% of the time. We calculated that we would need a maximum sample size of 3200, where p = 55%. Fifty-five per cent was our upper estimate of sexual violence in sex work [40]. The chi-squared statistic was 7.84 from this calculation.

To test for numerical differences between sub-populations–for example, how experiences and frequency of sexual violence, harms, reporting and attitudes to safety vary between gender, race, ethnicity, citizenship, sexual orientation, income and/or sex market–a larger sample size may be required. With a suitable numerical scale devised and tested, a smaller size may be sufficient.

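### The survey sizes 1,760 and 3,200 and the chi-squared value 7.84 cannot be derived from the stated alternative at 80% power, although both sizes err on the large side

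*Protocol article*

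**What the plan says.** Section 2.3.5 defines the test as one of "independence of outcome (binary Yes, No) and jurisdiction (4 levels) with 3 degrees of freedom". It then fixes the threshold: "Since a significance level of 5% is desired, the chi-squared statistic would need to exceed 7.81". Directly after that it states that "a minimum sample size of 1760 respondents for the survey would be required, with a minimum of 440 respondents in each jurisdiction".

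The next paragraph gives the alternative. The overall rate is set first: "We anticipated the overall probability of sexual violence at 15% across all 4 jurisdictions". The contrast follows: "with 2 jurisdictions differing by 10 points (ie. one records 10% and the other 20" per cent), and this is "to be detectable at least 80% of the time".

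The upper figure comes next: "We calculated that we would need a maximum sample size of 3200, where p = 55" per cent. The paragraph closes with "The chi-squared statistic was 7.84 from this calculation".

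The section names no power other than 80%, no allowance for unusable responses and no multiplicity adjustment. The four site rates behind the 55% case are not given. The Abstract and Work Package 1 in section 2.3 plan a survey of 1,000.

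**The concern.** A test, a level, a power and an alternative together determine a sample size. Section 2.3.5 states all four for the 15% case, so a reader should be able to recover its totals, and cannot. The reported statistic is a second warning sign. It lies just above the critical value of 7.81, yet 80% power requires the expected statistic to lie well above it.

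This paragraph is the only numerical basis for the study's main hypothesis. Sections 2.2.3 and 2.3.2 let the survey close once the sample is sufficient, and section 2.3.6 uses a mid-point look to direct further recruitment where it is not. None of these places gives a number, so a reader will turn to section 2.3.5. If its figures are wrong, the distance between the planned 1,000 and an adequate sample is misjudged.

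**Working it through.** **Inputs from section 2.3.5.** 3 df; 5% level; 80% power; overall rate 15%; one site at 10% and one at 20%; equal groups (4 × 440 = 1,760). With equal groups and an overall 15%, the other two sites must average 15%. Both are taken as 15%, since any spread between them would lower the required size.

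**Critical value.** The 95th percentile of chi-squared on 3 df is 7.815, so the plan's 7.81 is reproduced.

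**Formula.** The noncentrality is λ = N × w², where w² = mean of (pᵢ − p̄)² ÷ [p̄(1 − p̄)]. Power is the probability that a noncentral chi-squared variable (3 df, λ) exceeds 7.815. For 80% power λ must be 10.90; for 95% it must be 17.17.

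**15% case, 10/15/15/20%.**
- Mean squared deviation = (0.05² + 0 + 0 + 0.05²) ÷ 4 = 0.00125.
- w² = 0.00125 ÷ (0.15 × 0.85) = 0.009804.
- N for 80% = 10.9026 ÷ 0.009804 = 1,112.06, so 1,113, or 279 per site when rounded up (4 × 279 = 1,116).
- At 1,760: λ = 17.25, power 95.1%.

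**55% case, assumed 50/55/55/60%.**
- w² = 0.00125 ÷ (0.55 × 0.45) = 0.005051.
- N for 80% = 10.9026 ÷ 0.0050505 = 2,158.7, so 2,159, or 540 per site (4 × 540 = 2,160).
- At 3,200: λ = 16.16, power 93.7%.

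**Range over other 55% layouts with a 10-point difference (80% power).** The layout 50/50/60/60% needs about 1,080. One site 10 points above or below three at 55% needs 1,421 or about 1,450. All are below 2,159, and none comes near 3,200.

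**Could another single power level explain both sizes?**

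| Power | N at 10/15/15/20% | N at 50/55/55/60% |
|---|---|---|
| 80% | 1,113 | 2,159 |
| 90% | 1,446 | 2,806 |
| 95% | 1,752 | 3,400 |
| Stated | 1,760 | 3,200 |

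No row gives both. At 95% the first size nearly matches, but the second does not.

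**The statistic 7.84.** The text attaches it to 3,200 and 55%, where the expected value under the assumed layout is 16.16. At 50/55/55/60% a value of 7.84 belongs to N of about 1,553. Under the stated 15% alternative it belongs to N = 800 (800 × 0.009804 = 7.843), where power on 3 df is 64%.

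**Simulation (200,000 tables per case).** Power was 95.4% for 1,760 at 15%, 93.8% for 3,200 at 50/55/55/60%, and 64.9% for 800 at 15%. These agree with the formula.

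**Planned n = 1,000, 250 per site.** At 15%, λ = 9.80 and power is 75%. At 50/55/55/60%, λ = 5.05 and power is 44%.

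**The case against.** The strongest defence is that the plan promises at least 80% power and both sizes deliver it: 95% for 1,760 at 15%, and about 94% for 3,200 under the assumed 55% layout. That stands. The stated targets are not underpowered in their own scenarios, and the fault is that they cannot be derived from the inputs.

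The 55% site rates are indeed an assumption, so 2,159 is conditional on it. The range above shows that the mismatch with 3,200 does not depend on that choice. It is also fair that 1,760 appears before the alternative is introduced, with no power attached, so its link to the 15% case is a reading of the text.

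Two stronger readings are tempting, and the document supports neither.
- A reader might infer that the study was really sized at 800 with 64% power, and that 800 was later taken as a per-site number (4 × 800 = 3,200) with 1,760 = 0.55 × 3,200. The article never mentions 800. The value 7.84 also equals (1.96 + 0.84)², a quantity from a two-group calculation, and it also arises at N = 3,200 with 12.5/15/15/17.5%, which is not the stated contrast. Its origin cannot be established.
- A reader might say that 1,760 is too small for the 55% scenario. The plan gives 3,200 for that case, not 1,760.

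Lastly, section 2.3.6 tests the hypothesis by logistic regression in a non-random sample, and section 2.3.5 already says that subgroup comparisons may need more respondents. Both limit how literally any total should be taken. Neither explains the stated figures.

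**Conclusion.** The point holds as an arithmetic and reproducibility error. On the stated test and alternative, 1,760 exceeds the 80% requirement of 1,113 by 58% (1,760 ÷ 1,113 = 1.58). Under 50/55/55/60%, 3,200 exceeds 2,159 by 48% (3,200 ÷ 2,159 = 1.48), and by more under the other layouts tried. The statistic 7.84 is incompatible with 3,200 at 55% and a 10-point difference. Whatever its source, an expected statistic just above 7.81 does not give 80% power on 3 df, which needs 10.90.

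The error is conservative for the stated targets. It matters because it obscures the standing of the planned 1,000, which falls moderately short of 80% in the 15% case and far short under 50/55/55/60%.

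These results assume equal groups and, for the second scenario, the site rates named above. Unequal recruitment would change the totals; section 4.3 notes the small population in Northern Ireland.

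**What to change.** Rewrite the calculation in section 2.3.5:
- Use the noncentral chi-squared distribution on 3 df and list the four assumed rates for each scenario.
- Either replace 1,760/440 and 3,200 with the resulting totals (about 1,116, or 279 per jurisdiction, at 10/15/15/20%; about 2,160, or 540 per jurisdiction, at 50/55/55/60%), or keep the sizes and state the power they give (about 95% and 94%).
- Delete the sentence reporting 7.84.
- State the power of the planned 1,000 with equal groups (about 75% and 44%), and have sections 2.2.3 and 2.3.2 point to the corrected figure when they speak of a sufficient sample.

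Restating the calculation costs one paragraph and two cross-references. Adopting the 80% totals as recruitment targets is a separate decision with a real cost: compared with 1,000, it means 116 more respondents in the 15% case (1,116 − 1,000) and 1,160 more under 50/55/55/60% (2,160 − 1,000).
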